## Discussion

The increase prevalence of obesity and health inequalities in adults with intellectual disabilities is further accentuated by the limited access to evidence-based health care in meeting the equality legislation and addressing the health needs of this population group [45]. The need for research on the management of obesity for adults with intellectual disabilities has been emphasised as a priority for research and an important step towards addressing this issue [12, 13].

This pilot study will examine the feasibility of conducting a full-scale trial. The trial will help provide valuable insight into the feasibility of key issues such as the acceptability of randomisation and the fidelity of the intervention delivery.

Both arms of this trial are active interventions designed to support adults to make healthier lifestyle choices, with particularly focussed on supporting weight loss. This study will compare the two dietary strategies, an individualised EDD with quantitative dietary advice against a health education approach without quantitative dietary advice. Both interventions include support to increase physical activity and incorporate behaviour change techniques. Thus, comparing the two interventions will allow the identification of the essential and any superfluous components of the intervention which will be used to inform the optimal management approach to take forward in designing a full-scale clinical trial to address the obesity epidemic in adults with intellectual disabilities.

This study will make important contributions to the available evidence in this field, by piloting an intervention that fully satisfies UK clinical obesity guidelines on weight management. In a recent review of weight management interventions for adults with intellectual disabilities and obesity, it was reported that there are relatively few published studies and that the evidence available is subject to methodological limitations including recruiting small samples sizes with inadequate statistical power, and with only a few studies implementing a randomised controlled design [11]. None of the interventions met current recommendations from UK clinical guidelines on the use of multi-component interventions with an EDD for weight loss [12, 13]. Studies instead include combinations of a component relevant to supporting individuals to increase levels of physical activity, a dietary advice/health education components or a component with a focus on behavioural change. Furthermore, only a few studies were able to demonstrate a clinically significant weight loss of 5%–10% of initial body weight and met the recommended minimum follow-up period of 12 months to examine the effectiveness of a weight loss intervention.

Current guidelines on weight management interventions recommend weight maintenance as an integral component, illustrating that individuals who have lost a clinically significant weight loss and are able to maintain this weight have made substantial lifestyle changes that will prevent future weight gain or health risks [12, 13]. However, research for weight management in the general population and adults with intellectual disabilities has mainly focused on the development and evaluation of weight loss strategies and has not examined extensively the effectiveness of weight maintenance interventions that immediately follow a weight loss phase [46]. Only four studies involving participants with intellectual disabilities offered a structured weight loss maintenance intervention [24, 25, 47, 48]. Of these, only one study, reported the long-term effects of a 6-month weight maintenance intervention [45], illustrating that after 6 months, most adults with intellectual disabilities were able to sustain the clinically significant weight lost in phase 1 or continue further to lose weight. This study will therefore add to the evidence base by piloting a structured weight maintenance phase.

The controlled design is a key strength of this study, as it is considered the optimal design to evaluate complex interventions [49] and will add to the limited evidence of controlled studies of weight management interventions of adults with intellectual disabilities and obesity. There is limited evidence on which to base a best alternative control intervention. An ‘active’ control intervention is selected for this study over a non-intervention control; as in addition to the ethical issues discussed previously, the research group believes that this design would threaten the validity of the study by not taking into consideration the specific treatment effects of the intervention. In addition, it is believed that offering participants no intervention would have a negative effect on study recruitment and retention of participants. Receiving information on the importance of weight management may influence participants receiving a non-intervention control to change their behaviour and seek out other resources available in order to make healthier lifestyle choices. This could potentially cause individuals to drop out from the study and/or make it difficult to follow individuals up when offering them no intervention. The findings of this study will provide clear direction on this key issue and guide future experimental designs.

It is recognised that specific challenges are likely to arise when conducting research with adults with intellectual disabilities due to their cognitive and communication needs. In particular, it is noted that recruitment of adults with intellectual disabilities to research studies is challenging and is evident from the small sample sizes reported in previous research [11]. A review by Cleaver et al. [50] reported that ethical procedures which are consistent with this study such as the inability to contact potential participants directly and the procedures of taking consent may lead to poor participation in studies involving adults with intellectual disabilities. This study will assess the feasibility of recruiting and retaining adults with intellectual disabilities to a randomised design of a weight management intervention using a multi-point recruitment strategy which will collect information from recruitment sites such as organisations and services for adults with intellectual disabilities. This will be used to identify potential barriers and facilitators to recruitment which will help inform other controlled trials of weight management interventions and also be influential in informing the development a full-scale multi-centre clinical trial.

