Prior to this study, a single-stranded feasibility study was carried out to examine the efficacy of TAKE 5; a multi-component weight management intervention specifically designed for adults with intellectual disabilities and obesity [15, 16]. TAKE 5 was developed in collaboration with National Health Service (NHS) Greater Glasgow & Clyde Weight Management Service (GCWMS) [14] and modelled on their multi-component intervention, which incorporates diet and activity advice underpinned by behaviour change approaches and based on clinical guidelines [12, 13]. Full results from the TAKE 5 feasibility study have been published previously [15, 16]. The feasibility study found that TAKE 5 was acceptable to adults with intellectual disabilities, and carers, and reported clinically important reductions in body weight which were comparable to those achieved in adults with no reported intellectual disability following the GCWMS multi-component intervention [17]. Furthermore, clinically important reductions in risk factors associated with chronic diseases, such as waist circumference and increased physical activity levels, were also observed [15, 16, 18].

This study will add to the limited evidence base of controlled trials which have examined the efficacy of weight management interventions for adults with intellectual disabilities by piloting an intervention meeting current UK clinical recommendations on weight management. This study will compare the effects of a multi-component weight management intervention, TAKE 5 with a health education control intervention which does not include quantitative dietary advice to generate an individualised energy deficit, Waist Winners Too (WWToo). The design and rationale of the study with detail on the components of both interventions will be reported in this protocol.

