### Design

This study is a single-centre, single-blind pilot randomised trial. It consists of two active intervention arms: TAKE 5 multi-component weight management intervention versus treatment as usual (TAU), health educational intervention, WWToo. TAU in most areas in the UK for adults with intellectual disabilities and obesity is inconsistent—ranging from no intervention to the WWToo health education approach. An ‘active’ control intervention is preferred to the traditional non-intervention control group as due to the health risks associated with obesity [19, 20]; the research group believe it to be unethical to offer participants to be randomised to the control group with no intervention, for a 12-month period. Sixty-six participants will be randomised to the study (33 to each treatment arm) for a 12-month period; a 6-month weight loss period (comprising of 9–12 sessions designed to take place between two and three weekly intervals) followed by a 6-month weight maintenance period (comprising of six sessions taking place once a month). If the participants have not lost a clinically relevant weight loss of 5% of initial body weight at the end of the weight loss period, they will be advised to continue on the weight loss plan for a further 3 months, followed by a condensed 3-month weight maintenance period, mirroring the procedures conducted by the GCWMS and allowing a 12-month ‘intervention period’ for all participants. The study design is illustrated in Figure 1.

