### Sample size

There is limited data from controlled trials of weight management involving adults with intellectual disabilities on which to base a sample size calculation. This study is designed to estimate recruitment and retention rates for a full-scale clinical trial; it is not powered to detect a difference between study groups. Sixty-six participants will be recruited (33 to each treatment arm). This will provide sufficient insight into recruitment and retention rates, which will have a 95% confidence interval of no more than ±10%. The sample size will allow for a possible attrition rate of 20%. This study also aims to determine likely variance of study outcomes in order to power a larger randomised trial; if 50 participants provide outcome data at 12 months, a 90% confidence interval for each variance estimate will have a width of approximately 70% of the estimate (i.e. −26% to +44%).

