### Diet

#### Phase 1—weight loss

To achieve a healthy sustainable weight loss of 0.5–1.0 kg per week, a daily EDD of 600 kcal is recommended [11, 12]. Each individual’s daily energy deficit will be calculated based on the estimate of their total energy expenditure −2,510 kJ (600 kcal). Basal metabolic rate (BMR) will be calculated with gender, age, height and weight using the Mifflin St. Jeor equation [27]. Total energy expenditure is estimated from BMR multiplied by a physical activity level of 1.3 [28].

The EDD provides daily caloric intake from a specified number of daily portions from the five food groups in the *Eatwell* plate: starchy foods such as bread, rice, potatoes and pasta; meat/fish and alternatives; fruit and vegetables; milk and dairy products; foods high in sugar and fat [29]. The EDD also gives specific advice on portion sizes and alternatives to energy dense food stuffs.

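### The Discussion says that comparing TAKE 5 with WWToo will identify essential and superfluous components, but a two-arm comparison of packages that differ in several ways can estimate only the whole-package effect

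*Protocol article*

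**What the plan says.** The Discussion of the protocol article introduces the comparison with "This study will compare the two dietary strategies": an individualised energy-deficit diet with quantitative advice, against health education without it. It then notes that both arms support physical activity and use behaviour change techniques. From this it concludes, with the word 'Thus', that "comparing the two interventions will allow the identification of the essential and any superfluous components of the intervention". The rest of that sentence gives the finding a purpose: "which will be used to inform the optimal management approach to take forward in designing a full-scale clinical trial".

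The Background puts the aim differently. There the study will "compare the effects of a multi-component weight management intervention, TAKE 5 with a health education control intervention", although the same sentence goes on to single out the control's lack of quantitative dietary advice. The Design section says of the trial: "It consists of two active intervention arms". The Data analysis section describes a random-effects linear regression for weight change, with randomised group as the treatment term, adjusted for baseline weight and the minimisation variables.

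**The concern.** The Discussion sentence makes an inferential claim and gives it a use. To call a component essential or superfluous, one needs a comparison in which that component varies while the others do not. The intervention sections show that several components change together between the arms, and that others do not change at all.

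Taken at its word, the sentence invites two unsound conclusions. A weight difference in favour of TAKE 5 could be credited to the energy-deficit diet alone. A lack of difference could be taken to show that the extra elements of TAKE 5 are superfluous. Either could then influence what goes into the full-scale intervention.

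**Working it through.** No figure in the article bears on this point. The check sets the intervention sections side by side and asks what a two-arm comparison can identify.

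**Step 1: what differs between the arms.**

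| Component | TAKE 5 | WWToo |
|---|---|---|
| Diet, weight loss phase | Individualised energy deficit ("a daily EDD of 600 kcal is recommended") | Non-quantitative advice on food groups |
| Physical activity | Step targets and pedometer | Same activity guidelines, but no encouragement to monitor or raise step counts by pedometer |
| Behaviour change | Eight listed techniques, plus further ones such as problem solving where ability allows | Goal setting and self-monitoring, for diet and activity only |
| Maintenance phase | Six themed sessions, a new individual energy-balance plan, continued behavioural strategies including relapse prevention | Weighing, discussion of weight, opportunity for questions |

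Table 2 shows that session content also differs in both directions. WWToo has sessions on food labelling and alcohol. TAKE 5 covers emotions and overeating, cravings, and relapse prevention.

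**Step 2: what is shared.** Both arms have the same number of face-to-face sessions, delivery by a research dietitian, general activity guidance, goal setting and some self-monitoring.

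**Step 3: what can be estimated.** Let *μ* be the expected outcome under everything the arms share. Let *d*, *p*, *b* and *m* be the effects of the differences in diet, pedometer and step targets, behaviour techniques and maintenance content. In the simplest additive case:

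- mean in TAKE 5 = *μ* + *d* + *p* + *b* + *m*
- mean in WWToo = *μ*
- difference Δ = *d* + *p* + *b* + *m*

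That is five unknowns and two group means. Written as a design matrix for 33 + 33 participants, with an intercept and four component indicators, there are 5 columns. Every TAKE 5 row is (1, 1, 1, 1, 1) and every WWToo row is (1, 0, 0, 0, 0), so the rank is 2. One rank goes to the intercept and one to the sum Δ.

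The same Δ arises if *d* = Δ and the rest are zero, or if *b* = Δ and the rest are zero, or if a helpful component is partly offset by an unhelpful one. Δ = 0 does not imply that each term is zero. Adding participants repeats the same two rows and leaves the rank at 2. Interactions between components would add unknowns without adding contrasts.

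**Step 4: the shared components.** Their effects sit inside *μ* in both arms and cancel from Δ. The comparison says nothing about whether they are essential or superfluous.

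**Step 5: could the stated analysis help?** The planned model estimates a randomised-group effect. The further analyses mentioned concern baseline characteristics and their interaction with treatment, not intervention components. Component indicators that coincide exactly with arm cannot be separated by any choice of regression model.

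**The case against.** Three points can be made for the authors.

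**Diet is the main intended difference.** The Background sentence also singles out quantitative dietary advice, and the WWToo activity component follows the TAKE 5 guidelines apart from the pedometer and step element. This stands, and the correction should say that the packages differ mainly in diet. It does not rescue the sentence. The behaviour techniques and maintenance content also differ, and even a pure diet contrast would test that one element and leave the rest unsorted.

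**Component learning is planned elsewhere.** Under Process measures, the dietitian records after each session how well components worked, and also records attendance and success with behaviour techniques, to help develop the full-scale trial. This stands too, and such data may reasonably shape views on components. They are not the between-arm comparison that the Discussion credits, and the in-depth process evaluation is described as a separate study.

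**It is Discussion prose.** This is correct and limits the weight of the point. A reader might infer that the trial's conclusions or efficacy analysis depend on identifying components. The documents do not support that: no research question, outcome or model concerns components, and the Conclusion speaks of acceptability of randomisation, attrition and estimates of outcomes.

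A reader might also infer that the trouble is lack of precision, since the Sample size section says of the study that "it is not powered to detect a difference between study groups". That is a separate and openly stated limitation. Component effects would remain unidentified in a trial of any size.

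**Conclusion.** The statement is wrong as written. The design identifies one quantity, the effect of the TAKE 5 package against the WWToo package, and cannot attribute it to diet or to any other component. This rests only on the article's own description of the two interventions and on there being two randomised arms. It needs no assumption about variance, clustering or attrition.

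The consequence is small. It touches the stated interpretation and its stated use for the full-scale trial, and leaves the feasibility aims, sample size, outcomes and planned analysis unchanged. It is a correction worth making, not a defect in the pilot's design.

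**What to change.** Change one paragraph of the Discussion.

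1. Instead of describing a comparison of two dietary strategies, describe TAKE 5 and WWToo as whole packages that differ mainly, but not only, in quantitative dietary advice.
2. Replace the sentence beginning 'Thus' with: *The comparison estimates the effect of the TAKE 5 package versus WWToo and cannot by itself show which components are essential or superfluous; the process evaluation may inform views on individual components for the full-scale trial.*

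The cost is two wording changes. Interventions, data collection, sample size and analysis are unaffected, and the process data referred to are already planned.

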## Conclusion

There is limited access to evidence-based health care for adults with intellectual disabilities. Currently, no published controlled studies of weight management interventions for adults with intellectual disabilities meet clinical obesity recommendations. This pilot randomised trial will examine the acceptability of randomisation and attrition rates and provide pilot data on the estimates of patient-centred outcomes of TAKE 5 compared to the health education control intervention. If this study design is acceptable to adults with intellectual disabilities and shows a significant effect on outcome measures, this protocol can serve as a framework or model on which development of a full-scale clinical trial can be based.

## Trial status

Recruitment commenced in February 2014 and is projected to be complete by November 2014.

## Abbreviations

BMR: Basal metabolic rate
BMI: Body mass index
cpm: Counts per minute
EDD: Energy deficit diet
FSA: Food Standards Agency
GCWMS: Glasgow & Clyde Weight Management Service
ITT: Intention to treat
IVRS: Interactive voice response system
IPAQ-S: International Physical Activity Questionnaire-Short version
NHS: National Health Service
MRC: Medical Research Council
WWToo: Waist Winners Too
PARQ: Physical Activity Readiness Questionnaire
TAU: Treatment as usual.
